# Protocol Treatment

- 1. Treatment Schedule

Use actual weight or estimated dry weight if fluid retention Cycle 1 treatment = 28 days

All subsequent treatment cycles = 21 days (±3 days)

| Drug | Dose | Treatment | Retreatment |
| --- | --- | --- | --- |
| Ibrutinib | assigned at registration | PO daily (Day 1 to 28  of Cycle 1, then Day 1- 21* on subsequent cycles) | Every 21 days  (±3 days)  until confirmed progression |
| Pembrolizumab | 200 mg | IV injection on Day 8 of Cycle 1 and then Day 1 of each  subsequent cycle | Every 21 days (±3 days) until confirmed progression |

* Patients should receive a sufficient quantity of ibrutinib to last until the next scheduled treatment visit.

- 1. Determination of Maximum Tolerated Dose (MTD)
  2. Dose Escalation Scheme

| Dose level | Ibrutinib** |
| --- | --- |
| -1 | 140 mg |
| 0* | 280 mg |
| 1 | 420 mg |

* Starting dose level

** If the patient has clinical or laboratory evidence of liver failure during the treatment, then calculate the Child-Pugh score and adjust the ibrutinib dose (see Table 8.3).

NOTE: Doses will not be escalated in any individual patient.

- 1. MTD Determined

As of MCCC Amendment 6, the MTD has been determined to be Dose Level 1. Dose Level 1 will be used for the expansion cohort.

- 1. Dose Limiting Toxicities

Dose limiting toxicities (DLT) are defined to be:

| ***Toxicity*** | ***DLT Definition*** |
| --- | --- |
| Hematologic | Grade 4 ANC, Grade 4 Hgb, or PLT <25,000 |
| Renal | Serum creatinine ≥2 times baseline |
| Neurologic | ≥Grade 2 neurosensory or neuromotor toxicity |
| Other nonhematologic | ≥Grade 3 per NCI Common Terminology Criteria for Adverse Events (CTCAE) version 4.0* |

*Grade 3 rash or fever despite maximal supportive treatment(s) will be considered dose-limiting; all grade 4 rash and fever will be considered a DLT.

The maximum tolerated dose is defined as the highest dose level among those tested where at most one out of 6 patients develops a DLT prior to the start of their second cycle of treatment and the next highest dose level is such that 2 out of a maximum of 6 patients treated at this dose level developed a DLT prior to the start of their second cycle of treatment.

- 1. Dose escalation plan

NOTE: As of MCCC Amendment 6, the MTD has been determined to be Dose Level 1. A minimum of 2 or a maximum of 6 patients will be accrued to a given dose level.

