# Dosage Modification Based on Adverse Events

Strictly follow the modifications in this table for the first cycle, until individual treatment tolerance can be ascertained. Thereafter, these modifications should be regarded as guidelines to produce mild-to-moderate, but not debilitating, side effects. If multiple adverse events are seen, administer dose based on greatest reduction required for any single adverse event observed. Reductions or increases apply to treatment given in the preceding cycle and are based on adverse events observed since the prior dose.

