Subjects requiring the initiation of therapeutic anticoagulation therapy (eg, atrial fibrillation) should be monitored closely for signs and symptoms of bleeding and the risks and benefits of continuing ibrutinib treatment should be considered.

- - - **Dose modification for invasive procedures or surgery**

Ibrutinib may increase risk of bleeding with invasive procedures or surgery. The following guidance should be applied to the use of ibrutinib in the perioperative period for subjects who require surgical intervention or an invasive procedure while receiving ibrutinib:

- - - - For minor procedures (such as a central line placement, skin or needle biopsy, lumbar puncture [other than shunt reservoir access], thoracentesis, or paracentesis) ibrutinib should be held for at least 3 days prior to the procedure and should not be restarted at least 3 days after the procedure. For bone marrow biopsies, that are performed while the subject is on ibrutinib, it is not necessary to hold ibrutinib.
      - For any surgery or invasive procedure requiring sutures or staples for closure, ibrutinib should be held at least 7 days prior to the intervention (except for emergency procedures) and should be held at least 7 days after the procedure and restarted at the discretion of the investigator when the surgical site is reasonably healed without serosanguineous drainage or the need for drainage tubes.
    - **Dose modification for liver impairment subjects**

Ibrutinib is metabolized in the liver and therefore subjects with clinically significant hepatic impairment (Child- Pugh class B or C) are excluded from study participation in our initial phase 2 study, and lower starting dose was given in subjects with Child - Pugh Class A liver impairment (280 mg daily).

In this modified phase 1 study, patients with clinical evidence of liver impairement (Child – Pugh Class A, B, and C) at the time of screening are already excluded from particitipating, in addition to a lowered starting dose at 420 mg daily (compared to 520 mg in the initial study), to reduce any significant adverse effects. Therefore, for any liver impairment during the course of the treatment, the dose modification will follow the guideline in table 8.1 and 8.2, and no further modifications will be needed. It is critical for providers to monitor subjects for signs of toxicity and follow dose modification guidance as needed (Refer to Appendix 4 Table 8.1).

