- For subjects with existing chronic mild hepatic impairment (Child-Pugh class A) at enrollment, the starting dose has to be adjusted to a level of 280 mg daily (two capsules).
- For subjects who develop mild hepatic impairment while on study (Child-Pugh class A), the recommended dose reduction for ibrutinib/placebo is to a level of 280 mg daily (two capsules) unless lower doses had already been implemented.
- For subjects who develop moderate hepatic impairment while on study (Child-Pugh class B), the recommended dose reduction is to a level of 140 mg daily (one capsule).
  1. Overdose
- Subjects who develop severe hepatic impairment (Child-Pugh class C) must hold study drug until resolved to moderate impairment (Child-Pugh class B) or better.

Subjects who develop acute hepatic toxicity with liver enzymes Grade 3 or higher while on study should be managed per standard dose modification guidelines in Section 8.

There is no specific experience in the management of ibrutinib overdose in patients. No maximum tolerated dose (MTD) was reached in the Phase 1 study in which subjects received up to 12.5 mg/kg/day (1400 mg/day). Healthy subjects were exposed up to single dose of 1680 mg. One healthy subject experienced reversible Grade 4 hepatic enzyme increases (AST and ALT) after a dose of 1680 mg. Subjects who ingest more than the recommended dosage should be closely monitored and given appropriate supportive treatment.

Refer to Section 10.0 for further information regarding AE reporting.

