# Ancillary Treatment/Supportive Care

- 1. Full supportive care

Patients should receive full supportive care while on this study. This includes blood product support, antibiotic treatment, and treatment of other newly diagnosed or concurrent medical conditions. All blood products and concomitant medications such as antidiarrheals, analgesics, and/or antiemetics received from the first day of study treatment administration until 28 days after the final dose will be recorded in the medical records.

- 1. Hypersensitivity reactions

Patients do not require premedication prior to ibrutinib or Pembrolizumab treatment, as hypersensitivity reactions is not expected. In the unlikely event of a hypersensitivity reaction, treatment with antihistamines, H2 blockers, and corticosteroids is recommended. Patients should be pre-medicated with the typical regimen for subsequent cycles.

- 1. Concurrent enrollment in other trials

Patients may not enroll in a different clinical study, including Cancer Control studies, in which investigational procedures or agents are being used, while participating in this study.

- 1. Palliative radiation

Patients must terminate study treatment if they are to receive radiation therapy for palliative reasons as it impacts upon assessing response.

- 1. General patient monitoring and supportive care guidelines
  2. Patients should be carefully monitored during the treatment phase and then followed appropriately. Decisions for retreatment or dose modifications/interruption should follow the guidelines in Sections 8.2.
  3. Patients who have an ongoing study agent-related serious adverse event upon study completion or at discontinuation from the study will be contacted by the treating physician or his/her designee at least every 2 weeks until the event is resolved or determined to be irreversible.
  4. Side effect management for **PEMBROLIZUMAB** toxicities

These are to be regarded as guidelines for managing toxicity that occurs with pembrolizumab therapy and should not replace clinical judgement (i.e. - patients with Trade 1 rash may require systemic steroids).

- 1. Diarrhea

9.611 Grade 1- without abdominal pain/or blood in stool and symptoms, may be caused either by pembrolizumab or by ibrutinib. Infectious etiologies should be ruled out. Patients may be managed symptomatically, including the use of loperamide. Instruct patients to report any increase in stools.

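### Section 8.3 gives two incompatible ibrutinib rules for liver impairment that develops on study and does not say which one governs

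*Protocol*

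**What the plan says.** Protocol Section 8.3, under the heading on dose modification for liver impairment, explains that patients with Child-Pugh A, B or C impairment are excluded at screening and that the starting dose has been lowered. It concludes that for any liver impairment during treatment "the dose modification will follow the guideline in table 8.1 and 8.2, and no further modifications will be needed". Section 9.5 points the same way: "Decisions for retreatment or dose modifications/interruption should follow the guidelines in Sections 8.2".

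The bullets that follow in the same subsection set out a different scheme for impairment that arises on study:

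- Class A, where the dose named is 280 mg: "subjects who develop mild hepatic impairment while on study (Child-Pugh class A), the recommended dose reduction for ibrutinib/placebo is to a level".
- Class B: "subjects who develop moderate hepatic impairment while on study (Child-Pugh class B), the recommended dose reduction is to a level of 140 mg".
- Class C: patients "must hold study drug until resolved to moderate impairment (Child-Pugh class B) or better".

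The footnote to the dose escalation table in Section 7.2 supports this second scheme: "If the patient has clinical or laboratory evidence of liver failure during the treatment, then calculate the Child-Pugh score and adjust the ibrutinib dose".

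One sentence connects the two: "Subjects who develop acute hepatic toxicity with liver enzymes Grade 3 or higher while on study should be managed per standard dose modification guidelines". It names liver enzymes only. The opening of Section 8 adds that, where several adverse events occur, one should "administer dose based on greatest reduction required for any single adverse event observed".

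**The concern.** The first statement says Tables 8.1 and 8.2 are sufficient. The bullets directly after it prescribe further modifications. An investigator with a patient whose liver function worsens can follow either and be compliant with one and in breach of the other.

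What is at stake is exposure. Section 15.1 reports that, after a single dose, ibrutinib AUC was 2.7-, 8.2- and 9.8-fold higher in Child-Pugh A, B and C than with normal liver function, and Section 1 says lower doses are needed in clinically significant impairment. If Tables 8.1 and 8.2 govern alone, a patient who reaches class B or C can stay on the full dose in the situations shown below.

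The Child-Pugh scheme cannot simply be read as dead text. Section 7.2 relies on it, and the test schedule in Section 4.0 requires a Child-Pugh score at C2D1 and every later cycle. Those on-treatment scores have no dosing use if Tables 8.1 and 8.2 stand alone.

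**Working it through.** There is no planned figure to reproduce. The check is to run the same patient through both rules.

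**Inputs**
- Dose levels (Table 8.1): 420, 280, 140 mg.
- Table 8.2 hepatic row: AST, ALT and total bilirubin only. Grade 2 bilirubin is above 1.5 and below 3 x ULN: hold, then resume one level lower. Grade 3 is above 3 x ULN: discontinue both drugs.
- Table 8.2 applies only to events at least possibly related to study treatment (note at the head of Section 8.2). Its catch-all row covers non-laboratory events only.
- Appendix VII: five items at 1 to 3 points each; class A is 5-6, B is 7-9, C is 10-15. Three points are given for bilirubin above 3 mg/dL, albumin below 2.8 g/dL or INR above 2.30; two points for mild ascites.
- Assumption: bilirubin ULN of 1.0 to 1.3 mg/dL, as the protocol gives none.

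**Scores** (bilirubin + albumin + INR + ascites + encephalopathy)
- All normal: 1+1+1+1+1 = 5, class A.
- Any one laboratory item at 3 points: 3 + 4 x 1 = 7, class B.
- Albumin 2.5, INR 2.5, mild ascites: 1+3+3+2+1 = 10, class C.
- Bilirubin 4.0, albumin 2.5, INR 2.5: 3+3+3+1+1 = 11, class C.

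**Bilirubin grade at 4.0 mg/dL:** 4.0/1.3 = 3.08 and 4.0/1.0 = 4.0 x ULN, so Grade 3 across the assumed range.

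**Ibrutinib action for a patient on 420 mg**

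| Finding | Class | Tables 8.1/8.2 alone | Child-Pugh steps |
|---|---|---|---|
| (a) Albumin 2.5 only, or INR 2.5 only | B | 420 mg unchanged | 140 mg |
| (a) Albumin 2.5, INR 2.5, mild ascites | C | 420 mg unchanged | hold |
| (b) Unrelated bilirubin 4.0 only | B | 420 mg unchanged | 140 mg |
| (b) Unrelated bilirubin 4.0, albumin 2.5, INR 2.5 | C | 420 mg unchanged | hold |
| (c) Related bilirubin 4.0 only | B | discontinue | 140 mg |
| (c) Related bilirubin 4.0, albumin 2.5, INR 2.5 | C | discontinue | hold |

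Rows (a) assume that the finding is judged to be hepatic impairment, that it is not classed as immune-related (which has its own row in Table 8.2), and that the ascites is below Grade 3. A patient already at 280 mg would have 280 versus 140 mg in the class B rows of (a) and (b).

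**Where the rules agree on dose.** A related isolated bilirubin of 2.5 mg/dL is 2.5/1.3 = 1.92 to 2.5/1.0 = 2.5 x ULN, Grade 2, and scores 2 + 4 = 6, class A. Both rules lead to 280 mg; Table 8.2 adds a hold first.

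**Does any other sentence decide?** The enzyme sentence does not mention bilirubin, albumin or INR. The greatest-reduction sentence ranks adverse events against each other; it does not rank the table against the Child-Pugh steps. Section 9.5 repeats the pointer to Section 8.2 without addressing the bullets.

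**The case against.** The strongest reply is that much of the contrast is guidance against guidance. Section 8 makes the table strict only in the first cycle and treats it as a guideline afterwards, and the class A and B steps are recommendations. Only the class C hold is mandatory. This stands and limits the severity. It leaves room for judgment but does not reconcile the text. First-cycle strictness favours Table 8.2 in case (c), but is no help in (a) or (b), where the table has no row or does not apply.

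A second reply is that in (c) Table 8.2 is the stricter rule, and a patient already discontinued has no dose left to adjust. That is true if Table 8.2 is followed first. An investigator who follows the bullets would keep the patient on 140 mg or hold with a view to resuming, and the text does not exclude this.

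Third, (a) needs a judgment that liver impairment has developed; one low albumin is not liver failure in the sense of the Section 7.2 footnote. This also stands, and is why the condition is stated above.

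Fourth, the bullets look carried over: one mentions placebo in a single-arm trial, and another sets a starting dose for class A patients whom criterion 3.29k and Section 8.3 exclude. Deleting the bullets and the footnote would also end the contradiction. It would, however, leave patients in (a) and (b) at full dose despite the exposure figures in Section 15.1.

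A reader might also infer a conflict of 280 versus 140 mg for a related Grade 2 bilirubin that scores class B, for example 3.5 mg/dL at a ULN of 1.3 (2.69 x ULN, score 7). The documents do not support that. Table 8.2 holds ibrutinib until pembrolizumab resumes, which needs bilirubin at or below 1.5 x 1.3 = 1.95 mg/dL. That earns 1 point, for a score of 5 if nothing else is abnormal. The 280 mg and 140 mg doses belong to different liver states.

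**Conclusion.** The point holds. Section 8.3 contradicts itself on ibrutinib dosing for liver impairment that develops on study, and the Section 7.2 footnote sides with one of the two rules. From 420 mg, the rules part in cases (a), (b) and (c): unchanged versus 140 mg or hold in the first two, and discontinue versus 140 mg or hold in the third. Case (b) is plausible in this population: patients with liver metastases may enter with AST and ALT up to 5 x ULN (Section 3), and treatment continues for two cycles after first progression outside the CNS (Section 13.2).

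The conclusion rests on the current wording and the Appendix VII scoring. Only (c) uses an assumed bilirubin ULN, and it is stable from 1.0 to 1.3 mg/dL. How often class B or C would occur on study is not given and is not estimated.

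This is a patient-safety inconsistency that should be corrected. A reader might go further and infer harm to the sample size or the response estimate, or convert the AUC ratios into equivalent doses for a normal liver. The documents give no basis for either.

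**What to change.** In Section 8.3, strike the clause saying that no further modifications are needed, and state one rule:

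- Table 8.2 applies to events related to treatment.
- In addition, and regardless of attribution, a patient whose on-study hepatic impairment reaches Child-Pugh class B reduces ibrutinib to 140 mg, and one who reaches class C holds.
- Where both apply, the more restrictive action governs. Related Grade 3 or higher bilirubin or liver enzymes lead to discontinuation as in Table 8.2.

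Do not trigger on a change of score within class A. A normal liver already scores 5, and a fall in albumin from 3.6 to 3.4 g/dL moves the score only from 5 to 6; cutting 420 to 280 mg, a reduction of one third, would be out of proportion. Delete the on-study class A bullet or limit it to clinically judged hepatic impairment. Delete the class A enrollment bullet, which is void. Point the Section 7.2 footnote to the new rule.

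The cost is a text-only amendment. Section 4.0 already schedules the Child-Pugh score at baseline and from C2D1 at each cycle, with bilirubin, albumin and INR also drawn at C1D8. The small downside is that a few patients with impairment not caused by the drug will receive less ibrutinib.

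### Section 8.3 gives two conflicting dosing rules for liver impairment that develops on study: the same Child-Pugh B patient can stay at 420 mg under one and drop to 140 mg under the other

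*Protocol*

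**What the plan says.** Three places in the Protocol govern ibrutinib dosing when liver function worsens on study.

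- **Section 8.3, paragraph on liver impairment.** For any liver impairment during treatment, "the dose modification will follow the guideline in table 8.1 and 8.2, and no further modifications will be needed".
- **Section 8.3, the bullets that follow.** On developing class A, "the recommended dose reduction for ibrutinib/placebo is to a level of 280 mg daily (two capsules) unless lower doses had already been implemented". On developing class B, "the recommended dose reduction is to a level of 140 mg daily (one capsule"). In class C, patients "must hold study drug until resolved to moderate impairment (Child-Pugh class B) or better". A linking sentence reads: "Subjects who develop acute hepatic toxicity with liver enzymes Grade 3 or higher while on study should be managed per standard dose modification guidelines".
- **Section 7.2, footnote to the dose table.** If a patient has "clinical or laboratory evidence of liver failure during the treatment, then calculate the Child-Pugh score and adjust the ibrutinib dose (see Table 8.3").

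Table 8.1 sets the starting dose at 420 mg. The hepatic row of Table 8.2 is defined by AST, ALT and total bilirubin, together with immune-mediated hepatitis. Its residual row is limited to non-laboratory events. A note above the table confines all of it to events possibly, probably or definitely related to treatment. Section 4 schedules a Child-Pugh score before registration and on Day 1 of each cycle from Cycle 2.

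**The concern.** The paragraph says that Tables 8.1 and 8.2 are sufficient. The bullets and the Section 7.2 footnote then add a separate scheme based on a score that those tables do not use. Both are current text. A site with a patient whose Child-Pugh class has worsened can follow either one and be in line with part of the protocol.

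At stake is how much ibrutinib a patient with failing liver function receives. Section 1 says that ibrutinib metabolism depends on the liver and that impaired patients need lower doses. Section 15.1 reports single-dose AUC increases of 2.7-, 8.2- and 9.8-fold in Child-Pugh classes A, B and C compared with normal liver function.

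**Working it through.** The plan states no figure to reproduce here. The check applies both rules to the same patient.

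**Inputs**
- Appendix VII: five items, each 1 to 3 points. Albumin below 2.8 g/dL scores 3; INR 1.71–2.30 scores 2; bilirubin below 2 mg/dL scores 1; no ascites and no encephalopathy score 1 each. Class A is 5–6 points, B is 7–9, C is 10–15.
- Table 8.1: starting dose 420 mg.
- Table 8.2: triggers and relatedness condition as described above.

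**Case 1: score driven by albumin and INR.** Albumin 2.7 g/dL, INR 1.8, normal bilirubin, AST and ALT at Grade 0–1, no ascites, no encephalopathy, and no immune-related event diagnosed.
- Points (bilirubin + albumin + INR + ascites + encephalopathy) = 1 + 3 + 2 + 1 + 1 = 8, so class B.
- Tables 8.1/8.2: the hepatic row is not met, and low albumin or raised INR has no row. The residual row does not cover laboratory findings. Dose: 420 mg.
- Child-Pugh steps: 140 mg.
- Ratio: 420/140 = 3.0. For a patient who started at 280 mg it would be 280/140 = 2.0.

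The protocol gives no upper limit of normal (ULN) for bilirubin. If it is assumed to lie between 1.0 and 1.3 mg/dL, Table 8.2 Grade 2 begins above 1.5 × ULN, that is 1.5 to 1.95 mg/dL. A normal bilirubin stays below that throughout, so the example holds across the range.

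**Case 2: impairment judged unrelated to treatment, for example from liver metastases.** Table 8.2 does not apply at all.

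| On-study status | Tables 8.1/8.2 only | Child-Pugh steps |
|---|---|---|
| Class B from albumin/INR | 420 mg | 140 mg |
| Class B, cause unrelated | 420 mg | 140 mg |
| Class C, cause unrelated | 420 mg | hold |

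**How particular is Case 1?** Of the 3^5 = 243 item combinations, 90 give class B. In 45 of these, bilirubin scores 1 point, and in 6 of the 45 the score comes from albumin and/or INR alone. These are counts of combinations, not patient frequencies.

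**Exposure.** If the single-dose class B figure carries over, a patient left at 420 mg has about 8.2 times the AUC of a patient with a normal liver on the same 420 mg. The comparison is at one dose, so it needs no assumption about dose proportionality.

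**Starting point of the scale.** Five items at 1 point each give 5 points, which is already class A. The class alone therefore cannot show that a patient has developed class A impairment.

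**The case against.** Several points against this have force.

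- **Some text leans one way.** The opening of Section 8 says that with multiple adverse events the dose follows the greatest single reduction required, and Section 9.5 refers dose decisions to Section 8.2. But the first concerns several adverse events, not two schemes for one condition, and the second points to the less protective rule in Case 1. They pull in different directions and do not rank the rules.
- **Discretion.** Section 8 makes its table strict only in Cycle 1 and a guideline afterwards, and the first scheduled on-treatment Child-Pugh score is at Cycle 2 Day 1. The class A and B steps are only recommended. This weakens any charge of protocol violation. It does not remove the conflict: class C is a mandatory hold, and the Section 7.2 footnote is a directive.
- **Leftover text.** The bullets mention placebo, and one begins "For subjects with existing chronic mild hepatic impairment (Child-Pugh class A) at enrollment, the starting dose has to be adjusted", although exclusion 3.29k bars those patients. Deleting the bullets and the footnote would also restore consistency. Against that, the Child-Pugh score is still collected every cycle from Cycle 2, and deletion would leave the Case 1 patient at full dose.
- **Few patients.** This stands. Table 8.2 already catches related rises in AST, ALT or bilirubin, and its immune-related and non-laboratory rows can catch severe ascites or encephalopathy. Section 13 also lets the investigator stop for intercurrent illness.

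A reader might infer that the conflict also runs the other way: a related bilirubin above 3 × ULN stops treatment under Table 8.2 but could continue at 140 mg as class B, because the linking sentence names only enzymes. That is a strained reading. A recommended reduction does not naturally override a discontinuation, and Section 8's own principle is the greatest reduction.

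**Conclusion.** The contradiction is real and the text needs correcting. For a class B patient whose score comes from albumin and INR, or whose impairment is judged unrelated, the current wording supports both 420 mg and 140 mg. This assumes no earlier dose reduction and no other Table 8.2 event; the exposure figure also assumes that single-dose AUC ratios are a fair guide. With at most 23 patients in the study (Section 16, Sample Size), very few will meet the situation, and the primary endpoint is not materially affected. It is a patient-safety correction that should be made.

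Two stronger conclusions are tempting and are not supported.

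- **That the Child-Pugh trigger cannot be used.** The bullets speak of developing hepatic impairment, with the class as a severity label, and a normal liver scoring 5 has not developed impairment. The trigger is loose, and the different one in Section 7.2 (liver failure) adds to that, but a clinician can apply it.
- **That 140 mg in class B, or 280 mg in class A, is the wrong dose.** The protocol sets no exposure limit for hepatic dosing against which to test this. The doubling with food that Section 15.1 accepts is not such a limit.

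**What to change.** Amend Sections 7.2 and 8.3.

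1. In 8.3, delete the clause saying that no further modifications will be needed, and delete the class A starting-dose bullet.
2. Point the 7.2 footnote to the Child-Pugh steps in Section 8.3.
3. State that where both the Child-Pugh steps and Table 8.2 apply, the more restrictive governs, so that a Table 8.2 discontinuation always stands. This extends the greatest-reduction principle that already opens Section 8.
4. Use one trigger in both places: the steps apply when the Child-Pugh score worsens from baseline with clinical or laboratory evidence of hepatic impairment.

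Clerical tidying in the same amendment: Section 8.3 gives the initial dose as 520 mg where Section 1 has 560 mg; it cites a Table 8.1 in Appendix 4, but Appendix IV covers drug interactions; and the Table 8.3 named in the 7.2 footnote is not found under that name.

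The cost is a short dosing amendment with IRB review. No new visits, tests or drug supply are needed: the score is already taken at baseline and at each cycle from Cycle 2, and ibrutinib is supplied as 140 mg capsules. The downside is that a few patients will receive less ibrutinib.
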